## Abstract

**Introduction:**

Leptospirosis is a globally distributed zoonotic and environmentally mediated disease that has emerged as a major health problem in urban slums in developing countries. Its aetiological agent is bacteria of the genus *Leptospira*, which are mainly spread in the urine of infected rodents, especially in an environment where adequate sanitation facilities are lacking, and it is known that open sewers are key transmission sources of the disease. Therefore, we aim to evaluate the effectiveness of a simplified sewerage intervention in reducing the risk of exposure to contaminated environments and *Leptospira* infection and to characterise the transmission mechanisms involved.

**Methods and analysis:**

This matched quasi-experimental study design using non-randomised intervention and control clusters was designed to assess the effectiveness of an urban simplified sewerage intervention in the low-income communities of Salvador, Brazil. The intervention consists of household-level piped sewerage connections and community engagement and public involvement activities. A cohort of 1400 adult participants will be recruited and grouped into eight clusters consisting of four matched intervention-control pairs with approximately 175 individuals in each cluster in baseline. The primary outcome is the seroincidence of *Leptospira* infection assessed through five serological measurements: one preintervention (baseline) and four postintervention. As a secondary outcome, we will assess *Leptospira* load in soil, before and after the intervention. We will also assess *Leptospira* exposures before and after the intervention, through transmission modelling, accounting for residents' movement, contact with flooding, contaminated soil and water, and rat infestation, to examine whether and how routes of exposure for *Leptospira* change following the introduction of sanitation.

**Ethics and dissemination:**

This study protocol has been reviewed and approved by the ethics boards at the Federal University of Bahia and the Brazilian National Research Ethics Committee. Results will be disseminated through peer-reviewed publications and presentations to implementers, researchers and participating communities.

**Trial registration number:**

Brazilian Clinical Trials Registry (RBR-8cjjpgm).

STRENGTHS AND LIMITATIONS OF THIS STUDYThe first rigorous controlled intervention study for the effect of sanitation on *Leptospira* transmission in disadvantaged urban communities.This is a cluster-based non-randomised controlled trial with intervention clusters receiving a simplified sanitation intervention and matched control clusters no intervention.The alliance between the natural and social sciences and the potential that it has to deepen community perceptions about leptospirosis and interventions before and after, as well as involvement in it in some decision-making processes in the improvement of their health, well-being and sanitation.The allocation is non-randomised with selection based on intervention criteria determined by the implementer may have diluted intervention effects.Intervention will be carried out by the local public water and sanitation company, following their own planning, with no input or interference from the research team in the schedule or implementation.

## Introduction

Globally, leptospirosis is a leading zoonotic disease in terms of morbidity and mortality,^1^ causing >1 million cases and >50 000 deaths yearly.^1–3^ This zoonosis is an environmental and sanitation-related disease^4^ characterised by annual epidemics during periods of increased rainfall and flooding.^5 6^ Infection occurs frequently following exposure to water and soil that has been contaminated with the urine of infected animals.^3 7^ Leptospirosis is an emerging disease in urban areas of most low-income and middle-income countries,^1^ where a significant fraction of the population lives in disadvantaged urban communities (often called slums or *favelas* in Brazil).^8^ In those settings, poverty, precarious housing conditions, overpopulation and lack of basic sanitation enable a high density of rats (the main urban reservoir hosts^9–12^) and high leptospirosis transmission.^13 14^ As the population living in urban disadvantaged communities will double to 2 billion by 2025^15^ the burden of leptospirosis is expected to increase.

Public health intervention strategies to prevent leptospirosis transmission are essential and must target the infrastructure deficiencies to prevent or diminish human exposure to environmental contamination sources. Governmental interventions focused on improving sanitation are critical for reducing the burden of leptospirosis as well as other diseases, like diarrhoeal.^4 16^ However, these interventions, especially in disadvantaged urban communities, are not a priority or foreseeable soon considering the high cost of providing and maintaining such sanitation infrastructure. Exclusion of the disadvantaged urban communities’ health issues in the government’s political agenda,^17–19^ contributes to historical and structural disparities. Brazil, since the 80s, has been recognised as a global leader in the development of cost-effective water and sanitation systems for densely populated urban settings.^20 21^ These systems, called simplified or ‘condominial’ water and sewerage systems, are designed to be installed in densely populated, informal communities that are often situated in the kind of hilly terrain, common in Brazilian *favela* communities. The simplified sewerage approach is unique because it redefines the service unit as a community block rather than an individual household. It uses smaller pipes and inspection chambers (or cleanouts) at key junctions to facilitate installation and maintenance.^20 21^ The system design reduces costs by decreasing the length of the trenches needed for sewerage lines and by using smaller pipes made from less expensive materials such as polyvinyl chloride. The installation of this alternative system can cost 50%–70% less than a conventional system.^20^ The lower costs associated with the installation of simplified systems makes these systems a more feasible alternative to conventional sewer systems in poor, resource-constrained settings. However, the simplified sewerage approach requires intensive community mobilisation and engagement^22^ as it is residents who take on leadership roles and have responsibility for decision-making.

Health impact evaluations of simplified sewerage approach in preventing disease has previously been limited to diarrhoeal diseases.^23^ The evaluation of such interventions is challenging because of methodological problems such as cost and time of implementation, the requirement of large sample sizes, difficulties with randomisation of the intervention allocation, and confounding factors (eg, rodent infestation and social-economic status). Contact with environments contaminated with sewer overflow or residents’ exposure to open sewerage near the household can influence the degree of individual exposure to *Leptospira* bacteria.^13^ Humans exposure to *Leptospira* contamination through poor sanitation is mediated by individual behaviour, socioeconomic and environmental factors, rainfall and flooding. 4 Therefore, the mechanisms of *Leptospira* transmission have different but important components of the environmental transmission route, for which their relative contribution is unknown because of confounding factors. Only studies that integrate a rigorous characterisation of contamination sources (*Leptospira* load) and residents’ movement could separate their effects and understand how source reduction interventions impact those transmission mechanisms. Determining the contribution of each of these mechanisms to *Leptospira* infection would help us to simultaneously understand the relationships and pathways that drive transmission.^4^ This information is key to making interventions generalizable to other environmentally transmitted diseases that affect urban disadvantaged populations.

In this protocol, we describe an evaluation of a simplified sewerage intervention and community engagement with a quasi-experimental study design using non-randomised intervention and control clusters. We aim to assess the longitudinal impact of a simplified sewerage intervention on the incidence and transmission mechanisms of *Leptospira* infection. In addition, we intend to investigate the impact of these interventions on reducing other water and environmental-related transmissible diseases.

### Research aims and hypotheses

We hypothesise that the combination of a simplified sewerage infrastructure and community engagement activities will reduce the risk of *Leptospira* infection among disadvantaged urban communities in Salvador, Brazil. We further hypothesise that this approach will be effective in reducing: (1) frequency of human contact with open sewerage contaminated with pathogenic *Leptospira*; (2) rat infestation and (3) *Leptospira* load in the soil around the simplified sewerage. We aim to evaluate the efficacy of a sewerage intervention on reducing *Leptospira* infection and other health outcomes related to sanitation in disadvantaged urban communities in Brazil. Our specific objectives are to: (1) to evaluate prospectively the effectiveness of a simplified sewerage intervention in reducing the risk of *Leptospira* infection; (2) to determine the mechanisms by which the simplified sewerage reduce direct human contact with environmental pathogen load in urban slums. Figure 1 provides further details on our hypotheses concerning the effects of the sanitation intervention on the transmission mechanisms of urban leptospirosis. We conceptualise this protocol as focusing on the sanitation intervention to decrease leptospirosis; however, this study protocol generates rich opportunities to evaluate other health outcomes. Therefore, we additionally aim to investigate the effects of the sewerage intervention on childhood exposure to a range of enteropathogens, and long-term child neurodevelopment and anthropometry. As exploratory outcomes, we will also investigate the effect of the sewerage intervention on the reduction of risk of arbovirus infectious diseases.

**Figure 1 F1:**
[figure not shown]
Rationale, hypothesis and outcomes assessed in the study. We hypothesise that sanitation intervention will improve the environmental conditions and change the behaviour of humans, resulting in both direct and indirect impacts on the incidence of leptospirosis and other diseases human and well-being. HoH, household-level; qPCR, quantitative PCR.

## Methods and analysis

### Overview of study design

This is an intervention trial with a cluster non-randomised controlled trial, with eight clusters (four intervention and four control), including longitudinal serological follow-up of 1400 adults’ residents from disadvantaged urban communities at high risk for leptospirosis transmission in Salvador, Bahia, Brazil. The primary outcome will be *Leptospira* infection. Each pair of intervention and control clusters will be allocated in distinct hydrological sub-basins with distances from 1000 to 1500 m apart. Clusters will be matched on socioeconomic status (SES), topographic or hydrological characteristics, population density, and *Leptospira* seroprevalence. The cluster selection will also consider exposure to the pathogen by selecting houses that are located to similar distances to new sewerage system and control open sewers. The intervention aims at a combination of sanitation (simplified sewerage intervention) and community engagement activities.

### Study settings

Salvador is the third largest city in Brazil with a population of 2.9 million residents.^24^ Using a surveillance database of active leptospirosis in the study setting between 1996 and 2018, we performed a population-based, adjusted Kernel analysis among geo-localised records of households with leptospirosis cases to identify high-risk area corresponding to 8.06% of the total area of the city.^14 25^ We selected eight clusters (four intervention and four control) with average size 0.03 km^2^ located in these areas. The intervention clusters will be located in areas where the provision of simplified sewerage and community engagement is planned. Moreover, the choice of the control group is dependent on the implementer’s information regarding non-intervention planned in the area for a short-term period of 5 years. Geographic location of intervention and control clusters is detailed in figure 2.

**Figure 2 F2:**
[figure not shown]
Study clusters in the city of Salvador, Brazil. Altitude and sampling clusters (A). Example of baseline sanitation conditions of the study cluster (B). In (C) consort flow diagram by intervention and control cluster, data collection times and type of activities.

### Description of the sewerage intervention

During 2022 and 2023, the sewerage intervention (simplified sewerage intervention) will be implemented by the Public Water and Sanitation Bahia State Company (*Empresa Baiana de Águas e Saneamento*) in different urban locations in Salvador, Brazil. The expansion of the sanitation coverage in the city has generated an opportunity to assess the longitudinal effectiveness of the intervention on the transmission of sanitation-related diseases, such as leptospirosis. The company is government-owned, with responsibilities for managing, monitoring and distributing water and sanitation services throughout the state of Bahia. The costs, management and entire execution of the work will be the responsibility of the water and sanitation company, while the team of researchers will only monitor the development of the work.

This simplified sewerage intervention is characterised by receiving the sewage generated by a cluster of houses instead of individual houses. In conventional sewerage system designs, each household is connected directly to a principal line while in the sewer simplified system households are connected to branch lines within each block^23^ (online supplemental figure 1).

10.1136/bmjopen-2022-065009.supp1Supplementary data

The sanitation company will carry out the sewerage network works, which include the installation of a 150 mm primary pipe at the bottom of the residential lot, bordering a watercourse. Household sewerage networks are interconnected on one main line connecting to the main network, thus the intervention is expected to increase sanitation coverage in the study clusters by expanding the collection network. These interventions would exclusively be of a sewerage nature, with no complementary functions such as local drainage. Importantly, the intervention also includes community participation in the action designs and implementation.

### Community engagement

Simplified sewerage includes different degrees of social participation. We recognise that the intervention in sanitary sewerage impacts the local environment and the communities’ perception is affected by the sanitation interventions. Problems and failures related to sewerage intervention have been reported as mainly due to the difficulties in the relationship between the technicians who accompany the works and the communities which reduced the community participation to sewerage maintenance.^22^

Faced with this complexity related to urban sanitation, the community engagement processes that will be implemented in this study are focused on approaches that would stimulate community mobilisation to participate in the research processes, popular health education (PHE) actions, and in the evaluation of the implementation of sewerage intervention. PHE actions will be oriented toward disease prevention and health promotion of the population. The PHE is a ‘set of practices targeted at individuals and the community’,^26 27^ and this study intends to contribute to community empowerment and support for the management of sewerage intervention. The community engagement activities would be implemented in stages and with different stakeholders, including the community leaders, residents, and a multidisciplinary team of researchers including epidemiologists, ecologists, sanitation engineers, anthropologists, environmental microbiologists, geographers, economists, statisticians, etc. The study, therefore, aims to strengthen community participation in the decision-making in the management of sewerage intervention, and also support the involvement of residents in activities research such as (1) community and institutional mobilisation; (2) collaborative mapping and (3) PHE actions. Moreover, we will perform community ethnography to deepen the understanding of the social and cultural impacts caused before and after the intervention, as well as its environmental impacts and the mobilisation processes.

### Study population and sample size

To evaluate the effectiveness of the simplified sewerage intervention in reducing the risk of *Leptospira* infection, we plan to recruit an estimated 1400 participants aged ≥18 years, residing in the selected clusters (approximately 175 adults per cluster in baseline). To evaluate the intervention effect on secondary (sewerage contact, environmental pathogen load, long-term child development) and exploratory (arbovirus infections, diarrhoeal disease and enteric infection) outcomes, we plan to increase our sample size by 420 (30%) participants, aged between 6 months and 17 years, totalling 1840 people. We considered a potential loss to follow-up rate of 15%–20% per year. Therefore, by including additional participants, we ensure the maintenance of an appropriate sample size for the outcomes that will be studied. All participants from both intervention and control clusters will be followed over a period of 3 years after the sewerage intervention and a baseline prior to the intervention (figure 2). In the flow diagram, we provide a timeline and trial study phases in detail (figure 3).

**Figure 3 F3:**
[figure not shown]
Overview of the study procedures, the timeline for study and data collection. Note 1: Each cluster of the study will be formed by a cluster with intervention versus control. The period of activities for each serological survey will take place at the time described in the figure (allocation, recruitment and baseline). Note 2: Update years 1 to 5 will be realised after receipt of the water and sanitation company schedule.

The sample size was estimated using data on *Leptospira* infection from a previous leptospirosis cohort study in Salvador, Brazil.^13^ We divided the previous leptospirosis cohort study^13^ into areas of similar size to that the clusters used trial and calculated the between-cluster variation. Of 1840 individuals participating in the previous cohort, 142 (7.9%) experienced leptospiral infection (k/Intracluster Correlation Coefficient (ICC)=0.03). Power calculations are based on a cluster-level using effect sizes (% decrease in incidence between intervention and control clusters) 40%, 50% and 60%, assuming an infection rate of 0.08 per person-year. All sample size calculations used methods for matched cluster-randomised trials with the study structure of four matched pairs of clusters. Sample size estimates assumed a 12% annual drop-out rate across the 3-year study period.

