### Outcomes

#### Primary outcome measure

The study trial will consist of three specific phases: (1) baseline; (2) sanitation intervention implementation; (3) follow-up of the residents and evaluation of the sanitation intervention (figure 2). During the phase (1) a baseline survey will be conducted to characterise the demographics, SES and *Leptospira* seroprevalence in each cluster. During the phase (3) biannual serosurveys in the cohorts will be conducted to measure the primary outcome, *Leptospira* asymptomatic infection, and estimate the risk of infection during the dry and rainy seasons. The field team will collect blood samples from eligible participants with age ≥18 years. A blood sample (10 mL) will be collected from each study participant and examined for *Leptospira* antigen using the microscopic agglutination test diagnostic (MAT).^4^ MAT is the standard test to determine *Leptospira* infection in longitudinal studies and *Leptospira* infection will be defined as a fourfold rise in MAT titre or seroconversion (negative to ≥1:50) between samples from consecutive serosurveys. We will use a panel of six reference strains: representing *L. interrogans* serovars Autumnalis strain Akiyami A, Canicola strain H. Utrecht IV and Icterohaemorrhagiae strain RGA, *L. borgpetersenii* serovar Ballum strain MUS 127, *L. kirschneri* serovar Cynopteri strain 3522C and Grippothyphosa strain Duysterand the two clinical isolates: *L. interrogans* serovar Copenhageni strain Fiocruz L1-130 (isolated locally in 1996) and *L. santarosai* serogroup Shermani strain LV3954 (isolated locally). This procedure had the same performance in identifying MAT seroconversion in our prospective studies^4 14^ compared with the WHO recommended panel of 19 reference serovars. The screening will be performed with serum dilutions of 1:50–1:100. When agglutination is observed at 1:100, the sample will be titrated to determine the highest titre. As part of quality control procedures, two independent evaluations will be conducted for 8% of the samples and all samples from infected subjects.

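### The sample size assumes 12% annual drop-out while the same section considers 15%–20%; the 420 added minors give the adult cohort no reserve for the difference, and the printed total of 1840 should be 1820

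*Protocol article*

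**What the plan says.** All the figures stand in the protocol article under Study population and sample size, before and after the Figure 3 caption.

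- **Adult cohort.** For the infection outcome, "we plan to recruit an estimated 1400 participants aged ≥18 years", at about 175 per cluster in eight clusters.
- **Additional participants.** For the secondary and exploratory outcomes, "we plan to increase our sample size by 420 (30%) participants, aged between 6 months and 17 years, totalling 1840 people".
- **First loss rate.** The next sentence reads "We considered a potential loss to follow-up rate of 15%–20% per year".
- **Inference drawn from it.** The text continues: "Therefore, by including additional participants, we ensure the maintenance of an appropriate sample size for the outcomes that will be studied".
- **Second loss rate.** After the Figure 3 caption, the paragraph on the calculation ends: "Sample size estimates assumed a 12% annual drop-out rate across the 3-year study period".

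Under Primary outcome measure, the serosurveys are limited to adults: "The field team will collect blood samples from eligible participants with age ≥18 years". Under Eligibility and enrolment, children and adolescents aged 6 months to 17 years enter for the secondary outcomes.

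**The concern.** Three printed statements do not fit together.

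First, 12% lies outside the range of 15% to 20%. Both are rates per year for the same follow-up, and nothing assigns them to different populations or calls one a sensitivity case. The rate used in the calculation is the one that leaves more adults under observation.

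Second, the article answers the loss it has just mentioned by pointing to additional participants, and the only ones it describes are minors. They provide no blood sample for the primary outcome. A reader may conclude that the seroincidence comparison is protected against loss of 15% to 20%, when no adult reserve above 12% is described.

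Third, the two components do not add to the printed total.

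At stake are which attrition assumption governs the primary analysis, how many adults can be expected at the last serosurvey, and what the enrolment target is.

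**Working it through.** **1. The total**

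Inputs from Study population and sample size: 1400 adults, 420 minors (30%), total 1840.

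- 8 × 175 = 1400, which agrees with the text.
- 0.30 × 1400 = 420, which agrees with the text.
- 1400 + 420 = 1820. The printed 1840 is not reproduced; it is 20 too high.
- A total of 1840 would need 1840 − 1400 = 440 minors, and 440/1400 = 31.4%, not 30%.

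**2. Adults remaining after three years**

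With a constant annual loss d, the number remaining is 1400 × (1 − d)³.

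| Annual loss | Retained | Adults left | Per cluster | Fewer than at 12% |
|---|---|---|---|---|
| 12% | 0.88³ = 68.1% | 954 | 119 | – |
| 15% | 0.85³ = 61.4% | 860 | 107 | 94 |
| 20% | 0.80³ = 51.2% | 717 | 90 | 237 |

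If loss is instead taken as linear, 1400 × (1 − 3d), the numbers left are 896, 770 and 560.

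To keep the 954 completers implied by 12%, enrolment would have to be 1400 × 0.88³/(1 − d)³. That is about 1554 adults at 15% and about 1863 at 20%. These figures show the size of the gap. They are not a recommended target, because the number required before allowing for drop-out is not given.

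**3. Person-years**

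Averaging the number present at the start and end of each year, person-years per cluster are 175 × [0.5 + (1 − d) + (1 − d)² + 0.5(1 − d)³]:

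- 12%: 437
- 15%: 416 (about 5% fewer)
- 20%: 384 (about 12% fewer)

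The fall is smaller than the fall in completers because those lost still contribute time before they leave.

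**4. Illustrative power**

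From the article: control rate λ₀ = 0.08 per person-year, reductions of 40%, 50% and 60%, four matched pairs, and 0.03 for between-cluster variation. The article labels that 0.03 both k and ICC. Assumed here, because the article does not give them: two-sided alpha 0.05 and the Hayes–Bennett formula for matched pairs, with c − 2 = 2 in place of the number of pairs:

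z(power) = √{2(λ₀ − λ₁)² / [(λ₀ + λ₁)/y + k²(λ₀² + λ₁²)]} − 1.96, with y = person-years per cluster.

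For a 40% reduction, λ₁ = 0.048. With k = 0.03 and d = 12%:

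- sampling term: 0.128/436.6 = 0.000293
- between-cluster term: 0.0009 × (0.0064 + 0.002304) = 0.0000078
- z = √(0.002048/0.000301) − 1.96 = 0.65, so power is about 74%

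| Annual loss | 40% reduction, k = 0.03 | 50% reduction, k = 0.03 |
|---|---|---|
| 12% | 74% | 92% |
| 15% | 72% | 91% |
| 20% | 69% | 89% |

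If 0.03 is an ICC, k = √(0.03 × 0.92/0.08) = 0.587. For a 40% reduction the between-cluster term is then 0.00300 against a sampling term of 0.00029 to 0.00033, so it dominates, and moving from 12% to 20% loss changes power by under 1 point.

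**The case against.** Four points can fairly be made on the other side.

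- **The higher range is only a considered potential rate.** It need not be what the team expects, and could be a worst case or apply to the enlarged sample. This stands to the extent that the document does not show which rate is right. It does not remove the conflict, because no such distinction is written.
- **The sentence on additional participants may concern only the secondary and exploratory outcomes.** It directly follows the sentence listing them. This is a natural reading, and it rules out calling the sentence plainly false for the primary outcome. But the sentence refers to the outcomes to be studied without limit, and on the narrower reading the adults still have no described reserve above 12%.
- **An allowance is already built in.** This is correct. A reader might infer that the 1400 adults include no provision for loss, but the calculation assumed 12%. What is missing is cover for anything beyond that.
- **The error of 20 is small.** It is 1.1% of 1820 and does not touch the adult cohort. This also stands. It remains a wrong sum of two printed numbers, and no rounding explains it. The same figure, 1840, is given as the size of the previous cohort, but the article does not show that it was carried over.

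An article condenses a full protocol, but that does not dispose of the point. The concern is with figures that are printed and disagree, not with omitted detail.

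**Conclusion.** The inconsistency is real and should be corrected. The calculation uses 12% annual loss where the same section considers 15% to 20%. At the higher rates 94 to 237 fewer adults would complete three years than the calculation implies. The minors cannot make up that difference for the primary outcome, and the total is overstated by 20.

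The demonstrated effect on the design is modest: about 2 to 5 points of power for a 40% reduction and about 1 to 3 points for a 50% reduction. These figures rest on constant annual loss, two-sided alpha 0.05, the matched-pair rates formula and 0.03 read as k.

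A reader might infer that the stated power is too high or that the trial is underpowered. The article supports neither: it gives no alpha, target power or resulting power, so there is no stated figure to fault, and the slack in 1400 cannot be judged.

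**What to change.** 1. Reconcile the two statements to one annual loss rate. If they are meant for different purposes or populations, say so.
2. Rerun the adult calculation at 15% and 20% and report the resulting power with its alpha, stating whether 0.03 is k or an ICC.
3. Limit the sentence on additional participants to the secondary and exploratory outcomes that minors contribute to.
4. Correct the total to 1820, or, if 1840 is intended, correct 420 and 30% to 440 and 31.4%.

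The cost is one recalculation and a few edited sentences. The downside is that the reported power will rest on a slightly less favourable assumption. No change to recruitment follows from this point alone.
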